# Effects of Alternative Offers of Screening Sigmoidoscopy and Colonoscopy on Utilization and Yield of Endoscopic Screening for Colorectal Neoplasms: Protocol of the DARIO Randomized Trial

**DOI:** 10.2196/17516

**Published:** 2020-08-05

**Keywords:** cross-sectional study, prospective randomized controlled two-arm intervention trial, endoscopy, screening colonoscopy, screening sigmoidoscopy, neoplasms, liquid and tissue biobank, human biosamples, early detection markers, blood, stool, urine, saliva, tissue, prevention and early detection program

## Abstract

**Background:**

Flexible sigmoidoscopy and colonoscopy are recommended screening options for colorectal cancer (CRC). Despite colonoscopy being offered for CRC screening in Germany, the uptake of this offer has been very limited.

**Objective:**

The objective of this study was to assess the potential for increasing use of endoscopic CRC screening and the detection of advanced colorectal neoplasms by offering the choice between use of flexible sigmoidoscopy and colonoscopy.

**Methods:**

The DARIO study includes a cross-sectional study (part I), followed by a prospective 2-arm randomized controlled intervention trial (part II) with an associated biobank study (part III). Participation is possible in part I of the DARIO study only, parts I and II, or all 3 study parts. After obtaining informed consent from the municipalities, 12,000 people, aged 50-54 years, from the Rhine-Neckar region in Germany were randomly selected from residential lists of the responsible population registries and invited to complete a standardized questionnaire to investigate the nature, frequency, timing, and results of previous CRC screening and eventual diagnostic colonoscopies. In study part II participants from study part I with no colonoscopy in the preceding 5 years are randomized into 2 arms: arm A offering screening colonoscopy only, and arm B offering both options, either screening colonoscopy or screening sigmoidoscopy. The primary endpoint is the proportion of participants in whom colorectal neoplasms >0.5 cm are detected and removed at screening endoscopy. The secondary endpoints are the detection rate of any neoplasm and use of any endoscopic screening. Part III of the study will use samples from participants in study part II to construct a liquid and tissue biobank for the evaluation of less invasive methods of early detection of colon cancer and for the more detailed characterization of the detected neoplasms. Blood, urine, stool, and saliva samples are taken before the endoscopy. Tissue samples are obtained from the neoplasms removed during endoscopy.

**Results:**

A total of 10,568 from 12,000 randomly selected women and men aged 50-54 years living in the Rhine-Neckar-Region of Germany have been invited for participation. The remaining 1432 (11.93%) could not be invited because they reached the age of 55 at the time of contact. Of those invited, 2785/10,568 (26.35%) participated in study part I; 53.60% (1493/2785) of these participants were female. Study parts II and III are ongoing.

**Conclusions:**

This study will answer the question if alternative offers of either screening sigmoidoscopy or screening colonoscopy will increase utilization and effectiveness of endoscopic CRC screening compared with an exclusive offer of screening colonoscopy. In addition, alternative noninvasive screening tests will be developed and validated.

**Trial Registration:**

German Clinical Trials Register DRKS00018932; https://www.drks.de/drks_web/navigate.do? navigationId=trial.HTML&TRIAL_ID=DRKS00018932

**International Registered Report Identifier (IRRID):**

DERR1-10.2196/17516

## Introduction

### Background

Colorectal cancer (CRC) is the third most common cancer and the second most common cause of cancer deaths globally, responsible for more than 1.8 million cases and more than 800,000 deaths annually [1]. In Germany there are annually approximately 60,000 cases and 25,000 deaths as a result of CRC [2]. Slow progression of the cancer through the adenoma–carcinoma sequence opens up promising possibilities for prevention and early detection interventions [3].

The majority of CRC cases could be prevented by detection and removal of adenomas at screening sigmoidoscopy or colonoscopy [4]. Several countries provide an opportunistic screening programme including colonoscopy (Austria, Czech Republic, Greece, Iceland, Luxembourg, Portugal, Slovakia); in very few countries organized screening programs offer either colonoscopy (Germany, Poland) or sigmoidoscopy (England and Italy). The United States and South Korea offer both endoscopic screenings, reporting uptake of up to 60% [5]. Screening colonoscopy has the advantage that adenomas can be detected and removed in the entire colon and rectum but the procedure requires full bowel cleansing starting the day before colonoscopy. Screening sigmoidoscopy detects adenomas only in the distal colon and rectum (where the majority of CRCs occur), but is less invasive and less demanding regarding bowel preparation, with an enema immediately prior to the procedure being sufficient. Thus, adherence to the offer of screening sigmoidoscopy is expected to be higher than adherence to the offer of screening colonoscopy.

Severe complications during or after colonoscopy or sigmoidoscopy are very rare [6]. Besides, participants greatly benefit from the removal of advanced adenomas that would develop into CRC in about 30% of the carriers within the next 10 years [7,8]; participants also benefit from removal of nonadvanced adenomas, which are also targets of screening endoscopy with a somewhat lower CRC transition rate [8-10].

Several large-scale randomized trials have demonstrated a major reduction of CRC incidence and mortality by screening sigmoidoscopy [11-18]. Even larger effects are expected from screening colonoscopy, but first results from the only large-scale randomized controlled trial assessing this question will not be available before mid-2020. Evidence from epidemiological studies suggests that the majority of CRCs and CRC deaths could be prevented by detection and removal of adenomas by screening colonoscopy [15,19], with somewhat lower effects but better adherence to be expected from screening sigmoidoscopy [15,19-21]. Overall, low adherence is the major limiting factor for a more effective prevention of CRC incidence and mortality within the population. In Germany, screening colonoscopy (but not screening sigmoidoscopy) has been offered for women and men aged 55 and older since the end of 2002. However, only 20%-25% of those eligible have utilized this screening offer within the first 10 years [10].

### Objectives

The DARIO (German title: “Darmkrebsprävention: Innovative Wege am Nationalen Centrum für Tumorerkrankungen [NCT]) study includes 3 study parts (Figure 1) and has 3 major objectives: part I of the study, an epidemiological cross-sectional study that assesses through a standardized questionnaire in a random sample of women and men aged 50-54 years type, frequency, date, and results of previous early detection examinations and of potential diagnostic colonoscopies for CRC.

Part II of the study, a randomized intervention study including eligible participants from part I, randomizes those into 2 arms: arm A, in which a free screening colonoscopy alone is offered, and arm B, in which one of the two endoscopic screening options is offered: a free screening colonoscopy or a free screening sigmoidoscopy. The main objective of part II is to assess if and by how much the complementary offer of the less invasive screening sigmoidoscopy will lead to a higher number of detected and removed neoplasms (>0.5 cm). Endoscopies are performed at the Interdisciplinary Endoscopy Center (IEZ) of the Heidelberg University Hospital according to common clinical practice. Tissue samples are obtained from the neoplasms removed during endoscopy and will be banked for diagnostics and research purposes at the NCT tissue bank.

Part III of the study builds up a liquid biobank from biosamples (blood, urine, stool, saliva) of study part II participants, with samples taken prior to endoscopy. The main objective of study part III is the evaluation of less invasive methods of CRC screening and further characterization of detected neoplasms and defining biomarkers or biomarker panels of different composition (such as proteins, metabolites, DNA, microRNA, methylation markers) obtained via different -omics platforms.

**Figure 1 figure1:**
[figure not shown]
DARIO study design.

## Methods

### Study Design

The DARIO study is designed in 3 study parts: as a cross-sectional study (part I), followed by a prospective 2-arm randomized controlled intervention trial (part II) with an associated biobank study (part III) for biomarker evaluation as diagnostic tests of less invasive methods. The study design is shown in Figure 1. The trial was registered during recruitment of the participants in Deutsches Register Klinischer Studien on September 30, 2019.

### Study Part I: Cross-Sectional Screening for Previous Early Detection Examinations and Risk Factors

A total of 12,000 randomly selected potential participants aged 50-54 years living in the Rhine-Neckar region of Germany (main residence in Heidelberg, Mannheim, and Rhein-Neckar-Kreis, as defined by community codes) received a participant information document for study parts I + II and a short questionnaire by letter, and were invited by the DARIO study center at the National Center for Tumor Diseases in Heidelberg, Germany to participate in the study. Persons willing to participate were asked to sign and return the informed consent form for parts I + II of the study (included in the letter, together with a prepaid return envelope) and the questionnaire to the DARIO study center. The questionnaire includes questions on previous early detection examinations as well as questions concerning familial risk factors, lifestyle, health behavior, and nutritional factors.

Eligibility for parts II and III of the study is contingent on absence of a number of exclusion criteria that are specifically asked for in the questionnaire of part I. Exclusion criteria for parts II and III of the study are a history of CRC, a colonoscopy in the previous 5 years, a history of familial adenomatous polyposis or Lynch syndrome, and a severe illness which makes it impossible for the potential participant to visit the IEZ at the University Hospital Heidelberg or collaborating medical centers or gastroenterological practices in the Rhine-Neckar region (Heidelberg, Mannheim, and Rhein-Neckar-Kreis).

### Study Part II: Pre-Endoscopic Counseling and Endoscopic Screening in Study Arm A or B

Eligible participants are randomly allocated into either study arm A or B. Study arm A offers the participants a free screening colonoscopy, and in study arm B the eligible participants receive a letter, which offers the choice of either a free screening colonoscopy or a free screening sigmoidoscopy. The endoscopies take place at the IEZ or at other hospitals or medical centers or gastroenterological practices in the Rhine-Neckar region (Heidelberg, Mannheim, and Rhein-Neckar-Kreis).

To randomize the participants eligible for part II into arm A or arm B, a unique random number is generated for all 12,000 persons via a computer by a statistician with no involvement in the trial, before the persons are contacted in part I of the study, not knowing who will eventually participate in part I and who will be eligible for part II. Persons who agree to participate and who are eligible for part II are assigned into the respective study arm and a letter is sent to the participants inviting them to a pre-endoscopy counseling appointment at the NCT Study Center or at the IEZ. During pre-endoscopy consultation, the participants will receive routine patient information documents and, if they decide to have such an examination, they will sign the informed consent routinely used and required before endoscopy in clinical practice. Participants can be excluded from the study by the consulting physician due to underlying diseases or insufficient health status influencing endoscopy.

Screening colonoscopy and screening sigmoidoscopy are conducted at and under the responsibility of the performing center (hospitals, medical centers, or gastroenterological practices). Blinding of employees at the respective sites or at the study center is not feasible, because knowledge of endoscopy type(s) offered is a prerequisite for pre-endoscopy consultation and performing endoscopy. The study visit for the screening colonoscopy at the respective centers takes about 60 minutes for the screening colonoscopy and about 30 minutes for the screening sigmoidoscopy.

### Study Part III: Biosample Collection and Set up of a “Prevention Biorepository” for Biomarker Analysis

In conjunction with their visit for pre-endoscopy consultation at the NCT or IEZ, study participants willing to undergo endoscopy are informed in detail about study part III for which they are invited to donate biological samples (36 mL of blood, and samples of stool, urine, and saliva) for the evaluation of noninvasive or minimally invasive early detection markers. Biosamples are delivered directly to the Laboratory of the Division of Preventive Oncology at the NCT, the DARIO study center, without any delay. The stool sample is taken by the participants at their homes, collected prior to initiation of the large bowel preparation for colonoscopy, stored cool according to the manual, and delivered to the respective endoscopy center on the day of endoscopy. The sample reaches the NCT Laboratory on the same day and is processed and stored immediately. Exceptions occur with a maximum delay of 3 days for arrival or processing (eg, over weekends). The samples are then stored at 4°C for further processing or frozen directly at –80°C if no processing is required. All samples are processed according to the state-of-the-art standard operating procedures of the NCT Liquid Biobank, within 2-4 hours after taking the samples or entry of the biomaterial at the study center for the analysis of biomarkers. The samples are stored in barcoded vials and either frozen at –80°C or stored in liquid nitrogen for long-term storage. They are documented in a laboratory information management system (STARLIMS). For part III of the study, patients are asked to sign a separate specific informed consent form and a transfer agreement form for provision of biological samples.

### Data Collection and Documentation in the Coordinating Center

The unique participant number links biological samples, questionnaires, and endoscopy results. Information collected from endoscopy and histology reports is entered into a standardized study database by trained staff in the coordinating center at the NCT, using double data entry by 2 independent staff members. Data entries are checked through comparison of the corresponding data sets for inconsistencies and in case of differences in data sets, the data are validated by checking the original reports.

The information collected in the questionnaire in part I is documented by automated scanning of the questionnaires, optical verification of the scans by trained staff, and by applying comprehensive plausibility checks prior to statistical analysis. All collected information is stored at the coordinating center for at least 10 years after the end of the trial.

### Data and Biosample Analysis

Statistical analyses will be conducted using basic and advanced statistical methods for clinical epidemiological studies, including the analysis of biomarker data. The samples in the biobank built up in this trial will be used for determining the diagnostic value of novel biomarkers for early detection of colorectal neoplasms using standard receiver operating characteristic analyses for single markers and advanced biostatistics and bioinformatics tools for high-dimensional data obtained from -omics technologies.

The biospecimen will be used for identifying and evaluating biomarkers and biomarker signatures for cancer early detection and risk assessment. The most desirable highest scientific benefit from all biospecimen requires the determination of specific laboratory parameters and laboratory techniques according to the state of the art at the time of the analyses, which for most participants and most measurements will be years after recruitment. Examples of measurements anticipated at the time of conception of the DARIO study were measurements of defined metabolites in blood, stool, urine and saliva; circulating microRNA, especially in blood samples; single-nucleotide polymorphism analyses; next-generation sequencing; transcriptomics and application of several available and emerging -omics technologies, such as epigenomics, serolomics, proteomics, and stool metagenomics potentially related to the presence of early and advanced adenomas or colorectal carcinoma or both.

Long-term storage of the biosamples collected in this trial will enable timely validation of emerging promising early detection markers in the years to come.

### Method Against Bias

Data on confounding factors such as education, smoking, nutrition and diet, alcohol consumption, family history of cancer will be collected through the questionnaire in study part I. The trial is randomized to account for confounding factors. Extraction of clinical data from colonoscopy and pathology reports is accomplished in a blinded manner to avoid information bias. Data extraction and data entry (where applicable) are performed by 2 independent reviewers. Discrepant coding is resolved according to standard operating procedures to achieve the maximum accuracy possible. In addition, all recruiters and participants receive detailed instructions to ensure uniform collection and handling of biosamples. Preanalysis conditions, including sample transportation, are also documented to control for potential variation. All laboratory analyses are performed in a blinded fashion with respect to both treatment given and clinical/colonoscopy data.

### Sample Size Calculation

The current participation rate in the German screening colonoscopy program is 2%-3% per year among those eligible in the absence of personal invitations (performed as so-called opportunistic screening program). It has been repeatedly demonstrated (including own studies) that this participation rate can be at least doubled by personal invitation letters. Our estimates of recruitment numbers are rather conservative.

The sample size calculation is based on an anticipated participation rate of 25% (n=3000) in study part I out of 12,000 eligible participants and of 20% (n=2400) eligible participants for study part II, who are randomized into arm A or B (1200 participants in each arm).

In study arm A, 300/1200 participants (25.00%) are expected to undergo screening colonoscopy within 1 year, of whom 16.0% (48/300) are expected to have colorectal adenomas >0.5 cm detected and removed [22].

In study arm B, 240/1200 (20.00%) are expected to undergo screening colonoscopy and another 360/1200 (30.00%) are expected to undergo screening sigmoidoscopy within 1 year.

With an expected detection rate of neoplasms >0.5 cm of 16% and 12% by screening colonoscopy and screening sigmoidoscopy, respectively, the expected number of participants who have neoplasms >0.5 cm detected and removed is 81 (38 in arm A + 43 in arm B) [22,23].

The power to detect a significantly different rate of detection and removal of neoplasms >0.5 cm between both arms of study part II (48/1200 in arm A and 81/1200 in arm B) is 85% (two-sided chi-square test at α=.05).

As much as 90.0% (810/900) of participants undergoing endoscopy are expected to also participate in study part III. Evaluation of biomarker performance will be conducted according to standard methods of clinical epidemiology, bioinformatics, and biostatistics. Logistic regression models will be applied for individual biomarkers to construct prediction algorithm, and .632+ bootstrap [24] will be applied to adjust for potential overestimation of diagnostic performance. Areas under the receiver operating characteristic curves and their 95% confidence intervals, and sensitivity (true-positive rate) of each individual biomarker at cutoffs yielding 80% and 90% specificities (true‐negative rate) will be calculated.

In order to derive multimarker algorithms for the prediction of the presence of CRC, least absolute shrinkage and selection operator logistic regression models will be applied to markers that remain significant after multiple testing. The least absolute shrinkage and selection operator regression adapted to obtain models with the best prediction accuracy will be combined with .632+ bootstrap to adjust for overfitting. Prediction algorithms will be derived. Joint performance of biomarkers with known CRC risk factors (such as age, sex, family history, smoking, alcohol consumption, and dietary factors, information on which will be obtained from questionnaires) for predicting presence of neoplasms will additionally be evaluated in multivariable models. Analyses will be performed with statistical software R language and environment (version 3.5.3; R core team).

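### The multimarker LASSO is given presence of CRC as its outcome, but the part III cohort would hold only about 1 to 8 cancers, too few to fit or internally validate it reliably

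*Protocol article*

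**What the plan says.** The closing paragraph of the Sample Size Calculation section of the protocol article states the purpose of the multimarker analysis: "In order to derive multimarker algorithms for the prediction of the presence of CRC". For that purpose LASSO "logistic regression models will be applied to markers that remain significant after multiple testing", and the LASSO "will be combined with .632+ bootstrap to adjust for overfitting".

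Other statements of the biomarker target are wider. Data and Biosample Analysis says the biobank serves for "determining the diagnostic value of novel biomarkers for early detection of colorectal neoplasms". The last model in the LASSO paragraph combines markers with known risk factors "for predicting presence of neoplasms will additionally be evaluated in multivariable models". The Discussion also speaks of tests for colorectal neoplasms.

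On size, the same section says: "As much as 90.0% (810/900) of participants undergoing endoscopy are expected to also participate in study part III". The Study Part I section gives the age range of 50-54 years. It excludes from parts II and III anyone with a history of CRC, a colonoscopy in the previous 5 years, familial adenomatous polyposis or Lynch syndrome.

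**The concern.** The article treats adenomas and carcinoma as different lesions; Data and Biosample Analysis lists them separately. CRC and colorectal neoplasm are therefore two different outcomes. In a screening cohort of this age, neoplasms are common and cancers are rare. If the LASSO sentence is followed as written, marker selection after multiplicity correction, tuning of the penalty and the bootstrap correction for overfitting would all rest on a handful of cases. The resulting algorithm and its reported performance would depend on which few people happened to have cancer. If the sentence is loose wording, the outcome of a main part III analysis remains open and could be settled after the data have been seen.

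**Working it through.** **Inputs from the Sample Size Calculation section.** Endoscopies: 300 colonoscopies in arm A; 240 colonoscopies and 360 sigmoidoscopies in arm B. Detection of neoplasms >0.5 cm: 16% at colonoscopy, 12% at sigmoidoscopy. Part III uptake: 90%.

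**Plan's own figures.** 300 + 240 + 360 = 900 endoscopies, and 0.90 × 900 = 810, as stated. Expected participants with neoplasms >0.5 cm: 0.16 × 300 = 48 in arm A; 0.16 × 240 + 0.12 × 360 = 38.4 + 43.2 = 81.6 in arm B. The article gives 48 and 81. It labels the parts 38 and 43 as arms A and B, but by this arithmetic both belong to arm B.

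**Expected cancers.** The documents give no CRC prevalence, so it is an assumption p. Cases follow Binomial(810, p).

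| Assumed p | Expected cancers | P(no cancer) | P(10 or more) |
|---|---|---|---|
| 0.1% | 0.8 | 44% | below 0.1% |
| 0.2% | 1.6 | 20% | below 0.1% |
| 0.3% | 2.4 | 9% | below 0.1% |
| 0.5% | 4.1 | 2% | 0.9% |
| 1% | 8.1 | below 0.1% | 30% |

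An expected 10 cancers would need 10/810 = 1.23%; an expected 50 would need 6.2%. The plan uses the same 16% at colonoscopy for adenomas >0.5 cm and for neoplasms >0.5 cm. This leaves cancer only a rounding-sized share, which suggests the low end of the range but does not prove it.

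**Alternative count.** The Results section mentions 1060 participants screened by endoscopy. It is not clear that these are study endoscopies. If they were, 0.90 × 1060 = 954, giving about 1.0 to 9.5 cancers over the same range. The conclusion does not change.

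**Effect on the bootstrap.** In an ordinary resample of 810, the chance that none of e cases is drawn is (1 − e/810)^810: 37% for e = 1, 14% for e = 2, 2% for e = 4. The .632+ method also needs cases left out of the resample for testing. Each case is drawn with probability of about 0.632, so the chance that none is left out is about 0.632^e: 0.40 for e = 2 and 0.16 for e = 4.

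**Precision of discrimination.** With the Hanley-McNeil standard error and an assumed AUC of 0.80 among 810 people, the 95% half-width is about 0.26 with 4 cases, 0.19 with 8 and 0.05 with 116. This ignores the extra variability from marker selection and tuning.

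**Neoplasms >0.5 cm instead.** 0.90 × (48 + 38.4 + 43.2) = 116.6, about 117 cases. Colonoscopy participants alone: 0.90 × 0.16 × 540 = 77.8, about 78 cases among 0.90 × 540 = 486 people. The remaining 0.90 × 360 = 324 would have had sigmoidoscopy, which by the Background section detects adenomas only in the distal colon and rectum.

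**The case against.** **CRC may be shorthand.** Most statements of the part III aim cover precursor lesions, and the wider aims also speak of CRC screening and early detection of colon cancer. What is securely shown is then an inconsistent outcome label. That stands as a reading, but it still leaves an outcome that must be corrected, because the sentence as written ties the LASSO to CRC.

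**The article is condensed.** The full protocol is Multimedia Appendix 2 and is not shown, and laboratory methods are expected to be fixed years after recruitment. A missing cancer count or an unstated external source of cases is therefore no fault. The point rests only on the outcome that the article states.

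**The prevalence is assumed.** This is true, but the conclusion holds over a tenfold range.

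**Stronger readings do not hold.** A reader might infer that the model cannot be fitted at all. A penalised regression may still return a numerical solution with a few cases; the problem is reliability. A reader might also infer that the planned single-marker ROC curves and sensitivities at 80% and 90% specificity fail for the same reason. The article does not tie those to CRC: Data and Biosample Analysis gives their target as neoplasms. Nor does the stated 85% power support a neoplasm model; it concerns the comparison of arms A and B only.

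**The stakes are limited.** Part III is an associated biobank study, and no primary or secondary endpoint depends on the LASSO.

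**Conclusion.** The point holds for the multimarker LASSO and its .632+ step. As stated, their outcome is presence of CRC, which conflicts with the neoplasm outcome named elsewhere. At an assumed prevalence of 0.1% to 1%, it would supply about 1 to 8 cases among 810 participants. A CRC algorithm from this cohort alone could not be reliably fitted or internally validated. The same cohort would supply about 117 participants with a neoplasm >0.5 cm, provided that the plan's detection rates hold and that people with neoplasms join part III at the same 90% as others. The part II comparison is not affected. This should be changed before the biomarker analysis begins.

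**What to change.** Replace CRC by presence of a colorectal neoplasm >0.5 cm as the outcome of the multimarker LASSO and .632+ analysis, state the expected number of cases (about 117), and report marker values in any CRC cases descriptively.

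Add one sensitivity analysis, because non-cases after sigmoidoscopy have not had the proximal colon examined. Either restrict it to colonoscopy participants (about 78 expected cases) or restrict the outcome to distal lesions in all participants.

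The cost is a one-sentence change of outcome plus one further analysis, with no new data. The claim of a CRC-specific algorithm derived from this cohort is given up.

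### Part III: the marker significance screen appears to sit outside the .632+ bootstrap, so the multimarker AUC described as adjusted for overfitting would keep optimism from marker selection

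*Protocol article*

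**What the plan says.** The biomarker analysis is described at the end of the protocol article's Sample Size Calculation section.

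- Single markers: logistic models are fitted to individual biomarkers, and "632+ bootstrap [24] will be applied to adjust for potential overestimation of diagnostic performance".
- Multimarker models: "In order to derive multimarker algorithms for the prediction of the presence of CRC", the plan is that "least absolute shrinkage and selection operator logistic regression models will be applied to markers that remain significant after multiple testing". The LASSO regression "will be combined with .632+ bootstrap to adjust for overfitting".
- Size: "As much as 90.0% (810/900) of participants undergoing endoscopy are expected to also participate in study part III".
- Candidate markers: the Data and Biosample Analysis section foresees "advanced biostatistics and bioinformatics tools for high-dimensional data obtained from -omics technologies". It gives no number of markers.

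The article does not say whether the significance screen is repeated in each bootstrap sample or run once beforehand. It names no multiplicity method, gives no expected number of CRC cases, and describes no separate validation set for the multimarker model.

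**The concern.** The order given is screen, then LASSO, then bootstrap, and the bootstrap is attached to the LASSO. The screened markers are described as one fixed set, whereas a screen inside the resampling would give a different set each time. On that reading, every person left out of a bootstrap sample has already influenced which markers are in the model. The out-of-bag AUC is then not out of sample, and the .632+ estimate corrects coefficient fitting but not selection.

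Multiplicity control limits how many false markers pass. It does not remove the upward bias in the apparent strength of those that do. The bootstrap is the only protection against overfitting that the article describes for the multimarker model, so a weak panel could be carried forward on an AUC labelled as corrected.

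**Working it through.** **The plan's own figures.** The article gives no figure for biomarker accuracy. Its nearby figures reproduce:

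- Part III size: 0.90 × 900 = 810.
- Neoplasms >0.5 cm, from "With an expected detection rate of neoplasms >0.5 cm of 16% and 12% by screening colonoscopy and screening sigmoidoscopy, respectively": arm A 48; arm B 240 × 0.16 + 360 × 0.12 = 38.4 + 43.2 = 81.6. Expected in part III: 810 × (48 + 81.6)/900 = 116.6, if uptake of part III does not depend on the finding.
- Part II power ("48/1200 in arm A and 81/1200 in arm B) is 85"%): p1 = 0.04, p2 = 0.0675, pooled SE 0.00921, unpooled SE 0.00919; z = (0.0275 − 1.96 × 0.00921)/0.00919 = 1.03, power 0.848. This agrees, and the present point does not depend on it.

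**The estimator.** Let app be the apparent AUC and oob the out-of-bag AUC, not allowed below 0.5. Then R = (app − oob)/(app − 0.5), w = 0.632/(1 − 0.368R), and the .632+ estimate is (1 − w) × app + w × oob. If the markers were chosen on everyone, oob stays close to app, R is near 0, and the estimate stays near app.

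**Simulation A.** 810 people, 116 cases, 500 independent markers (assumed), t-test screen, L1 logistic regression with a fixed penalty, 40 resamples, true AUC from independent data. Averages are over data sets in which at least one marker passed. BH is Benjamini-Hochberg at 5%.

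| Scenario | Panel arose | Screen outside | Screen in each resample | True | Excess, outside | Error, repeated |
|---|---|---|---|---|---|---|
| 10 markers at 0.25 SD, BH | 25/40 | 0.657 | 0.596 | 0.583 | +0.074 | +0.013 |
| Same, Bonferroni | 23/40 | 0.636 | 0.585 | 0.576 | +0.060 | +0.009 |
| 10 markers at 0.4 SD, BH | 30/30 | 0.797 | 0.733 | 0.772 | +0.025 | −0.039 |
| No signal, BH | 22/400 | 0.621 | 0.534 | 0.503 | +0.118 | +0.031 |
| No signal, Bonferroni | 19/400 | 0.615 | 0.543 | 0.498 | +0.117 | +0.045 |

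With the screen outside, the correction does little. For the weak BH case the apparent AUC is 0.662, so the optimism is 0.662 − 0.583 = 0.079, of which .632+ removes 0.662 − 0.657 = 0.005. For the strong case it removes 0.812 − 0.797 = 0.015 of 0.812 − 0.772 = 0.040.

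**Simulation B.** Separate code, 117 cases, 1000 independent markers, BH at 5%, 120 data sets with 30 stratified resamples each.

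| Scenario | Screen outside | Repeated | True | Excess, outside | Error, repeated |
|---|---|---|---|---|---|
| 10 markers at 0.25 SD | 0.65 | 0.58 | 0.58 | +0.07 | 0.00 |
| 20 markers at 0.3 SD | 0.74 | 0.67 | 0.68 | +0.06 | −0.01 |
| 10 markers at 0.4 SD | 0.78 | 0.70 | 0.75 | +0.03 | −0.05 |

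With pure noise (200 data sets, a simplified linear LASSO), a panel arose in 7% and gave 0.62 against 0.50.

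**CRC as the target.** The article gives no case number. With 8 cases assumed, in Simulation A's set-up with BH:

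- Ten markers at 0.4 SD: 0.854 outside, 0.642 repeated, 0.548 true. Excess 0.306 outside and 0.094 repeated; a panel arose in 14 of 200 runs.
- No signal: 0.870 outside, 0.689 repeated, 0.502 true. Excess 0.368 outside and 0.187 repeated; a panel arose in 8 of 300 runs.

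**The case against.** The strongest reply is that the article never says the screen is run once on the full data. Which steps lie inside a resampling loop is detail that a condensed article may leave to the full protocol, which is an appendix not shown here. This stands as a limit: the bias is conditional on the plain reading. It does not dispose of the point, because the article fixes an order and names the LASSO as what is bootstrapped.

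A reader might infer more than the documents support:

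- *That the bootstrap is used only with the LASSO.* It is also used for the single-marker models. That corrects each model taken alone, not the choice of winners among many, so it does not cure the problem.
- *That a worthless panel will routinely look promising.* With no signal, the planned multiplicity adjustment leaves no panel in roughly 93% to 95% of data sets. It matters: an unadjusted p < 0.05 screen, which is not planned, gave 0.745 against a true 0.499.
- *That the simulated sizes are this trial's bias.* The cases are neoplasms, while the multimarker sentence targets CRC. Marker number, independence and effect sizes are assumed.
- *That this AUC is the final product.* The abstract speaks of developing and validating tests, and stored samples are meant to allow later validation of markers, although no validation set for this model is described.

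It also stands that repeating the screen is not free of error. With strong markers it is further from the truth (−0.039 and −0.05) than the screen outside (+0.025 and +0.03).

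**Conclusion.** The concern holds conditionally. If the analysis follows the plain reading, the multimarker AUC presented as adjusted for overfitting keeps selection optimism. With about 116 neoplasm cases and a multiplicity-adjusted screen, the excess is about 0.06 to 0.075 with weak markers and 0.025 to 0.03 with strong ones. With no signal it is about 0.12, in the 5% to 7% of data sets that yield a panel.

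Two separate simulations agree on direction and approximate size. Both assume independent markers, and several rows rest on few runs, so the values are approximate. CRC cases are likely far fewer than 116, so the bias could be larger; the 8-case figures only illustrate this.

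The point is worth correcting but confined to part III. The randomized comparison, its primary endpoint and its power are untouched.

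**What to change.** State that significance screening (with its multiplicity adjustment), penalty tuning and LASSO fitting are all repeated within every .632+ resample, and describe only the resulting AUC as corrected for overfitting. Say also how a resample in which no marker passes is scored; Simulation A used 0.5. If the full protocol already intends this, one sentence in the analysis description settles the matter.

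The cost is more computing time and lower reported AUCs, which can understate the truth by about 0.04 to 0.05 when markers are strong. With very few CRC cases, repeating the screen reduces the bias but does not remove it: about 0.09 to 0.19 remained with 8 cases assumed. Any such panel should therefore be reported as needing confirmation in independent samples.
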